### Eligibility criteria

#### Inclusion criteria

Eligibility criteria will include the following: [1] women aged 19–70 years; [2] patients with histologically confirmed stage I, II, and III breast cancer; [3] medically suitable for evaluation and participation in exercise intervention; [4] no evidence of distant metastasis or locally recurrent breast cancer; and [5] ability to understand and provide written informed consent in the Korean language.

**Table 1 Tab1:** Flow diagram for the schedule of enrollment, interventions, and assessments

TIME POINT	VISIT 1	VISIT 2 *[Phase 1]*	VISIT 3 *[Phase 1]*	VISIT 4 *[Phase 2]*	VISIT 5 *[Phase 3]*
	Baseline, (Before surgery)	POD 1	1 month from the baseline (± 2 weeks)	6 months from the baseline (± 1 month)	12 months from the baseline (± 1 month)

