#### Sample size

The calculation for sample size was based on a previous study that evaluated the effects of 16 week mixed strength and endurance exercise on insulin levels in patients with breast cancer [31]. Based on a power of 80%, two-sided statistical significance level of 5%, and medium-sized effect size, the minimum required sample size would be 80 participants. Considering the dropout rate to be 20%, 96 patients with breast cancer are needed for the current study.

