#### Anthropometric parameters and physical activity (PA)

[The evaluation schedule: at baseline, 1 month from the baselines (± 2 weeks), 6 months from the baseline (± 1 month), and 12 months (± 1 month)]. Body composition and Body mass index will be measured using InBody (BIO-SPACE®, InBody 720, Korea). The PA of participants will be measured using the Global Physical Activity Questionnaire (GPAQ), developed by the World Health Organization (WHO). It asks for any PA (including exercise) performed for at least 10 min during a typical week. Respondents will also report the time spent in PA performed at the workplace, transport, recreation, and sedentary behavior. The reliability and validity of the Korean GPAQ were examined in a previous study [39]. We will calculate PA as metabolic equivalent (METs) based on the GPAQ. Surgical complications that occurred within 30 days after surgery will be monitored through chart review. Surgical complications include surgical infection, wound complications (e.g., hematoma, wound dehiscence), seroma, and reoperation after breast cancer surgery.

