#### Statistical analysis methods

All analyses will be performed using the SPSS version 26.0 software (IBM Corp., Armonk, NY, USA). A Chi-square test for categorical variables and an independent t-test for continuous variables will be used to test group differences at baseline. Two-way repeated-measures ANOVAs will be conducted to observe the effects of the intervention on fasting insulin levels, shoulder ROM and function, body composition, inflammatory markers, microbiome, QOL, and physical activity levels. Paired t-tests will be performed to examine the difference between outcome measurements and baseline values, while independent t-tests will be employed to examine group differences in variables at each time point. The Bonferroni correction method will be used to correct for multiple tests. Analysis of covariance (ANCOVA) will be applied to test the effect of an exercise intervention on body composition, PA, and complications, since these variables will be measured after adjusting for baseline values. First, from baseline to 1 month from the baseline will be calculated and then the differences between groups will be examined after adjusting for baseline values and surgical methods. The same methods will be used for 6 and 12 months.

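### The baseline-adjusted ANCOVA, repeated at 6 and 12 months, does not fit surgical complications, which have no baseline value and are collected only to 30 days (minor)

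*Protocol article*

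**What the plan says.** Under Statistical analysis methods, the article says that "Analysis of covariance (ANCOVA) will be applied to test the effect of an exercise intervention on body composition, PA, and complications". The reason given is "since these variables will be measured after adjusting for baseline values". The model is then described: a quantity running from baseline to 1 month is calculated (the noun is missing, but a change score is evidently meant), and "the differences between groups will be examined after adjusting for baseline values and surgical methods". The paragraph ends: "The same methods will be used for 6 and 12 months".

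The variable is defined under Anthropometric parameters and physical activity (PA): "Surgical complications that occurred within 30 days after surgery will be monitored through chart review". The list follows: "Surgical complications include surgical infection, wound complications (e.g., hematoma, wound dehiscence), seroma, and reoperation after breast cancer surgery". Body composition, physical activity and complications are described together there, and the same three appear in the ANCOVA sentence, so it is clear which complications are meant.

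Table 1 places the baseline visit before surgery. No other method is named for complications. The chi-square test is named only for group differences at baseline.

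**The concern.** Body composition and physical activity are measured before surgery and again at 1, 6 and 12 months, so a baseline-adjusted change model suits them. Complications share none of these features. They are events caused by the operation, so they cannot be present before it, and their window closes at 30 days. The article names a method, a reason and three time points for this outcome, and its own definition and schedule conflict with the reason, the baseline covariate and the two later time points.

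The exercise programme starts on post-operative day 1, and this is the surgical harm outcome that the article describes. If the sentence is carried into the analysis as written, the analyst must improvise: drop a covariate, and decide what a 6- or 12-month result would mean. The same 30-day events could then be reported three times as if they were three results.

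**Working it through.** The article gives no event rate and no power for complications, so there is no stated figure to reproduce. The check concerns the structure of the model, followed by its behaviour at assumed rates.

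**Inputs from the article.** 96 participants allocated 1:1, so 96 / 2 = 48 per arm; two-sided 5% level; baseline before surgery; events counted to 30 days; covariates baseline value and surgical method.

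**Assumptions.** Each patient is scored 1 for any complication and 0 for none; two types of surgery, 40% of patients in one of them; event rates as shown below; no dropout.

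**1. Baseline covariate.** The model has four columns: intercept, group, surgical method, baseline complications. The last is 0 for all 96 patients, so the matrix has rank 3. The baseline coefficient cannot be estimated. The change score is Y − 0 = Y, the event itself. Neither result depends on the event rate, and both hold equally if complications are counted per patient.

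**2. Time points.** The 30-day window has closed well before the 6-month visit (± 1 month). Any analysis at 6 or 12 months can only reuse the same events.

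**3. Events expected.** 48 × 5% = 2.4 per arm; 48 × 10% = 4.8; 48 × 20% = 9.6.

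**4. The model that remains.** Without the baseline term, this is a least-squares model of a 0/1 outcome on group and surgical method. Its group coefficient is a risk difference adjusted for surgical method. Simulation under no group effect, 10,000 trials per row (overall rate = 0.6 × first + 0.4 × second):

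| Event rate by surgery type | Overall rate | Type I error | Trials with a negative fitted risk |
|---|---|---|---|
| 1% / 3% | 1.8% | 0.9% | 62% |
| 3% / 8% | 5.0% | 4.5% | 39% |
| 5% / 15% | 9.0% | 4.8% | 20% |
| 10% / 30% | 18.0% | 5.2% | 5% |
| 20% / 40% | 28.0% | 5.3% | 0.2% |

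Further simulations at single overall rates of 5%, 10% and 20% gave type I errors of 3.5%, 4.9% and 5.1%, with about 95% coverage of the interval for the risk difference. At about 2%, type I error fell to 1.2% and coverage to 85%. The chance of no event at all among 96 patients at 2% is 0.98^96 = 0.144. Such a trial yields no usable interval, so if it counts as a miss, coverage cannot exceed 1 − 0.144 = 0.856. That accounts for nearly all of the shortfall.

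**5. Choice of replacement.** In the same kind of simulation, Fisher's exact test had a type I error of 0.7% to 2.5%. Its power for 5% v 15% was 23%, against 37% for the linear model.

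**The case against.** The strongest reply is that this is careless drafting with little consequence. A constant covariate makes only its own coefficient inestimable; software drops it and the group contrast survives. ANCOVA needs a covariate, not necessarily a baseline value of the outcome, and surgical method is one that applies to complications. Most of this stands.

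A reader might infer that the model cannot be fitted, that its standard errors are wrong, or that it yields no risk difference. The documents and the calculations do not support this. The group coefficient is a risk difference, and its error rate and coverage are close to nominal at assumed rates of 5% to 20%. A confidence limit below zero is no defect for a difference in risks; negative values are impossible only for the fitted risks.

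It can also be said that the closing sentence on 6 and 12 months covers only what is measured then. That is a possible reading, but the sentence carries no such restriction, and complications stand in the list to which it refers.

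Two further limits are fair. That the outcome is binary is inferred from the list of events. And it would go too far to say that the trial has no proper safety analysis: a journal article condenses the full protocol, which may hold more. Complications appear in neither the objectives nor Table 1.

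The objection does not reach the core. The stated reason, the baseline covariate and the later time points do not apply to this variable at any event rate.

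**Conclusion.** The point holds as a minor error of specification. The ANCOVA sentence assigns complications a baseline adjustment that is constant at 0 and two later time points that have no outcome. This follows from the article's own definition and schedule and needs no assumed rate.

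The practical effect depends on the rate, which the article does not give. At 5% to 20% the reduced model's group comparison is roughly valid, though impossible fitted risks are common at the lower end. At about 2% the test is very conservative and in about one trial in seven (0.144) there would be nothing to estimate. These figures rest on 48 per arm, the assumed 40% split by surgery type and a yes/no outcome. Fasting insulin, the primary outcome, is unaffected.

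**What to change.** Remove complications from the ANCOVA sentence and from the 6- and 12-month repeats. In their place, specify one comparison between arms:

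- **Outcome:** the proportion of patients with any listed surgical complication within 30 days after surgery. Count it on that window and not at the 1-month visit, which is timed from the pre-surgery baseline with a margin of 2 weeks and can fall before day 30.
- **Main estimate:** the risk difference with a score 95% confidence interval, such as Newcombe or Miettinen-Nurminen. Fisher's exact test should not lead, because it is conservative at this sample size.
- **Support:** logistic regression adjusted for surgical method, penalised (Firth) if events are few.
- **Description:** each complication type listed by arm.

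The cost is wording only: no change to data collection, visits or sample size.

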## Results

### Discussion

Most patients with breast cancer undergo intense cancer treatments, including surgery, chemotherapy, and hormone therapy, depending on the stage and subtypes of cancer. These treatments result in shoulder dysfunction [28], cardiotoxicity [45], fatigue [46], sarcopenia, and insulin resistance [47], which are known determinants of poor QoL and prognosis [48]. Supervised exercise has been identified as a viable and supplemental approach for the rehabilitation of patients with breast cancer [49]. Numerous studies have shown that exercise has a significant clinical benefit in patients with breast cancer and have recommended engaging in regular exercise. Exercise is an alternative approach for mitigating the negative effects of cancer treatment and functional limitations [50, 51]. However, most previous studies have investigated the benefits of exercise on the above-mentioned outcomes in patients with breast cancer before, during, or after adjuvant chemoradiation therapy as separate studies in different samples. Moreover, there is a lack of information on exercise programs for patients with cancer during and following treatment periods for health maintenance. It is logical to think that tailored exercises should be applied to breast cancer patients because most breast cancer patients experience different treatment side effects after surgery. Therefore, we aimed to test the efficacy of a tailored exercise program, based on three different recovery phases (i.e., Phase I [surgery to 1 month], Phase II [1 month to 6 months], and Phase III [7 months to 12 months]), in the same research participants on insulin resistance as well as other symptom-related health outcomes.

During Phase I (surgery to 1 month), the most prevalent comorbidity following breast cancer surgery is poor shoulder function, including a decrease in ROM and impaired strength [52]. One recent study showed that recovery of ROM differs by surgery type; however, shoulder strength was reduced regardless of the surgery type [28]. It was also reported that reduced shoulder strength in the unaffected arm suggests reduced shoulder strength in both the affected and unaffected arms due to lack of utilization [28]. A recent study found that shoulder ROM and strength recover to pre-surgery levels within 1 month after surgery if a proper exercise program is implemented [35]. Taken together, these studies suggest that exercises focused on the recovery of shoulder function should be emphasized during this phase.

During the chemotherapy period (phase 2), patients with breast cancer typically experience muscle mass loss [53], insomnia [54], cardiotoxicities [45], and fatigue [46]. Exercise intervention improves these parameters [55] and the recent American Society of Clinical Oncology guidelines clearly recommend oncology providers recommend aerobic and resistance exercises during active treatment with curative intent to mitigate the side effects of cancer treatment [51]. Furthermore, exercise intervention during chemotherapy may improve the chemotherapy completion rate [56] and reduce the hospitalization rate [57], although the effect of exercise on chemotherapy completion remains controversial [58]. Furthermore, during hormone therapy, more than 60% of patients experience joint and muscle pain [59], which can be improved through proper exercise [60]. Although exercise could be beneficial for breast cancer survivors during this period, shoulder dysfunction, fatigue, and low fitness levels could be barriers to exercise. Therefore, exercise programs during this period should be tailored to the patients’ physical condition with the aim of maintaining muscle mass and fitness.

During the first year after cancer surgery (Phase III), most patients with breast cancer experience an increase in fat mass and decreased muscle mass, insulin resistance, and the risk of recurrence and mortality [61, 62]. In addition, fasting C-peptide levels in patients with breast cancer are associated with a 35% increased risk of death due to breast cancer [63]. Exercise is an effective self-management tool associated with body composition and reduced fasting insulin levels among breast cancer survivors [31, 33, 64, 65]. Thus, the effects of exercise on breast cancer outcomes may be mediated by insulin resistance and inflammatory markers. The intervention duration in most exercise intervention studies for cancer survivors was less than 6 months, and these studies implemented exercise after the completion of adjuvant therapies. In this regard, the exercise program developed for this trial tailored the exercise program to patients’ physical conditions, and cancer treatment-related symptoms were unique. Thus, our results will add new knowledge to existing knowledge.

Our study adds new knowledge in several aspects. First, our tailored exercise intervention will improve insulin resistance and would confirm the factors responsible for such improvement. Second, this trial will measure the microbiome of patients with breast cancer, which may be correlated with prognosis [66–68], along with other biomarkers. Therefore, the outcome of this trial will provide a clear explanation for changes in other physiological and psychological outcomes via changes in the microbiome. In addition, this randomized study will show that exercise programs according to phases of cancer trajectory have important clinical implications. It might influence patients’ lifestyle modification by changing their perceptions; hence, cost-effectiveness outcomes of patients’ lifestyle modification could potentially be expected.

## Conclusion

In summary, this trial is the first long-term tailored home-based exercise oncology trial to understand the long-term effects of exercise on fasting insulin levels, a surrogate indicator of cancer as well as an important indicator of metabolic health. The results of this trial highlight the importance of developing tailored exercise programs according to the phases of the cancer trajectory for patients with breast cancer, which will ultimately help with their recovery. These findings related to the program according to phases of cancer trajectory may represent a method of reducing breast cancer morbidity and mortality by increasing exercise and other positive effects. Therefore, tailored home-based exercises could have positive effects on a patient’s general condition.

## Data Availability

Not applicable.

## Abbreviations

ANCOVA: Analysis of covariance
GPAQ: Global Physical Activity Questionnaire
hs-CRP: High-sensitivity C-reactive protein
MVIC: Maximal voluntary isometric contraction
PA: Physical activity
POD: Post-operative day
QOL: Quality of life
RCT: Randomized controlled trial
ROM: Range of motion
SPADI: Shoulder pain and disability index
